### 6.3.4 Secondary analyses

For comparison, the results for the primary endpoint will also be given for the comparison of the "general osteopathic treatment group" vs. the "specific osteopathic treatment", and the "general osteopathic treatment group" vs. the "no treatment group". Bilateral tests will be realized at a 1.33% level (instead of 5%) in order to take into account the multiplicity induced by these two sensitivity analyses.

The final composite criteria (at M6) for neck and trapezius pain, headache and the 4 studied scores of quality of life (physical functioning, energy/well-being, body image, respiratory symptoms) will be analyzed using the same strategy as for the primary endpoint.

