## 6.2. Number of subjects required

Total number of patients planned: n = 32

Number of patients receiving general osteopathic treatment (group 1): n=16

Number of patients receiving specific osteopathic treatment (sham treatment)(group 2 ): n=8

Number of patients for the untreated control group (group 3): n = 8

We recall that this is a pilot study, in the case of a rare disease, "justifying" the small number of patients planned. However, the number of subjects should make it possible to have 80% power to demonstrate a difference of about one standard deviation of the mean VAS for pain in the group treated by general osteopathy versus the two other groups (treated by specific osteopathy or untreated (performing bilateral test with a significance level of 5%).

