### 6.3.3 Main analysis

The comparison will be made between the "general osteopathic treatment" group and the combination of the two "specific osteopathic (sham) treatment" and "no treatment" groups.

The final composite endpoint (at M6) for chest and back pain will be compared using a linear mixed model with random intercept at the individual patient level in the context of Mixed Model for Repeated Measurements (MMR). This type of model can take into account the correlation of data for the same patient. Bilateral tests will be made at a 5% level.

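### The 1.33% level set for the two pairwise comparisons follows from no standard correction for two tests at 5%; it is stricter than needed and should be 2.5%, with the method and the test family named.

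*Combined protocol and SAP*

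**What the plan says.** All references are to the combined protocol and SAP.

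- Section 6.3.3 (Main analysis) defines one primary comparison, general osteopathy against the sham and untreated groups combined. Its level is given as: "Bilateral tests will be made at a 5% level".
- Section 6.3.4 (Secondary analyses) adds two comparisons on the same endpoint, general against sham and general against no treatment. It sets their level and gives the reason: "Bilateral tests will be realized at a 1.33% level (instead of 5%) in order to take into account the multiplicity induced by these two" analyses. It names no method and shows no derivation.
- Section 6.2 (Number of subjects required) plans "Number of patients receiving general osteopathic treatment (group 1): n=16" and "Number of patients receiving specific osteopathic treatment (sham treatment)(group 2 ): n=8". The untreated group also has 8, for a total of 32. The power statement, "80% power to demonstrate a difference of about one standard deviation of the mean VAS for pain", refers to the general group against the other two groups.

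**The concern.** The stated reason and the stated number do not agree. The reason is that two extra tests are made, but the level is well below what two tests require, and below what three would require.

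At stake is the threshold that decides whether the report may call either pairwise difference significant. General against sham matters most for interpretation: section 2 keeps patient and investigator unaware of allocation only between groups 1 and 2, and the endpoint in section 6.1.1 is patient-reported pain. An over-strict level costs power in a contrast with only 8 controls, and a reader cannot reconstruct where the level came from.

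**Working it through.** **Inputs.** Level 1.33% two-sided and two comparisons (6.3.4); primary level 5% two-sided (6.3.3); groups of 16, 8 and 8 and a difference of about 1 SD (6.2). The plan states no effect size for the pairwise contrasts, so 1 SD is carried over as an assumption. No dropout rate is stated and none is applied.

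**Step 1: the plan's sample size.** For 16 versus 16 (8 + 8) at 1 SD, the noncentrality is 1/√(1/16 + 1/16) = 2.83. Power is Φ(2.83 − 1.96) = 80.7% by the normal approximation, or 78.1% by the noncentral t. The power claim in 6.2 reproduces.

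**Step 2: the 1.33% level.** Bonferroni is 0.05/m and Sidak is 1 − 0.95^(1/m).

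| Tests counted (m) | Bonferroni | Sidak |
| --- | --- | --- |
| 2 (the two pairs) | 2.50% | 2.53% |
| 3 (adding the pooled test) | 1.67% | 1.70% |
| 4 | 1.25% | 1.27% |

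Dunnett for two comparisons sharing the 16-patient arm: the correlation is (1/16)/(1/16 + 1/8) = 1/3. The two-sided level per test is 2.60% (normal) or about 2.63% (t, 29 df). With the pooled test added and the actual correlations among all three used, simulation gives a common level of about 2.35%.

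The plan's 1.33% is not reproduced. As a Bonferroni level it would need 0.05/0.0133 = 3.76 tests.

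**Step 3: error actually spent on the two tests at 1.33%.** Upper bound 2 × 1.33% = 2.66%. If independent, 1 − (1 − 0.0133)² = 2.64%. With correlation 1/3, 2.59% (normal) or about 2.55% (t, 29 df, simulated).

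**Step 4: power of a 16 versus 8 contrast at 1 SD.** The noncentrality is 1/√(1/16 + 1/8) = 2.31.

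| Calculation | 1.33% | 2.5% | Loss |
| --- | --- | --- | --- |
| t, 29 df (variance from all three groups) | 38.7% | 48.7% | 10.0 points |
| t, 22 df (two groups only) | 37.2% | 47.5% | 10.3 points |
| Normal approximation | 43.4% | 52.7% | 9.3 points |

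The relative loss is 10.0/48.7, about a fifth. For true differences of 0.8 to 1.5 SD the loss is about 7 to 10 points by the t calculation. The difference detectable with 80% power (22 df) is 1.55 SD at 1.33% and 1.42 SD at 2.5%. The results are the same for general against no treatment, which has the same group sizes.

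**Step 5: all three tests together, no gate, all means equal (simulated, 29 df).** The chance of at least one significant result among the pooled test at 5% and the two pairs is 5.7% with the pairs at 1.33%, and 6.9% with the pairs at 2.5%.

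**Step 6: closed testing as an alternative (simulated, 29 df).** Each pair is tested at 5% only if the pooled test is significant at 5%. The familywise error with all means equal is 4.1%. Power for a 1 SD difference from sham depends on the difference from no treatment: 58.5% if that is also 1 SD, about 47% if it is 0.5 SD, and 27% if it is 0.

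**The case against.** The best defence is that little depends on this number. The two contrasts are secondary and are described as sensitivity analyses in what section 6.2 calls a pilot study. The level errs on the safe side, biases no estimate, and leaves the primary test alone. All of this stands, and it limits the severity. It does not explain the number.

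Four stronger readings are tempting, and the documents do not support them.

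- **That the level costs a third of the power.** That compares 38.7% with the 58.5% of a gated procedure which the plan does not use, in its favourable case. Against a plain two-test correction the loss is about a fifth.
- **That general against sham is the weakest contrast.** It is the only blinded one, but general against no treatment is also 16 versus 8, so power is equal at an equal effect. The plan states no expected effect for either.
- **That the level is why these contrasts are weak.** Power is still only 47% to 53% at 2.5%. The main cause is the 8-patient arms.
- **That splitting alpha at all is a mistake because closed testing exists.** Closed testing is valid, but with no difference from the untreated group its 27% power is below the 38.7% of the present rule. It is a design choice.

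It is also an inference that the plan aims at 5% overall for the two tests. Section 6.3.4 says only that 1.33% replaces 5% because of multiplicity. Even so, no familywise target is stated that would produce 1.33%.

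**Conclusion.** The point holds as a should-fix. The level in section 6.3.4 does not follow from the reason given for it: two tests at 5% call for 2.5% to about 2.6% each, and even three call for 1.67% to 1.70% by Bonferroni or Sidak. The error is conservative, with about 2.5% spent over the two tests, and the primary test is unaffected. Its cost is about 10 percentage points of power per pairwise contrast at 1 SD.

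The power figures rest on the assumed 1 SD, no dropout, and a simple comparison of group means. Section 6.3.3 specifies a repeated-measures mixed model, so they are approximate. The mismatch in the level depends on none of these assumptions. Where 1.33% came from cannot be determined from the documents.

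**What to change.** In section 6.3.4, replace 1.33% with 2.5% two-sided per comparison and name the method (Bonferroni for two tests; Holm or Dunnett would also serve if named). State that the family is the two pairwise comparisons only, separate from the pooled primary test at 5%. If the sponsor has a reason for 1.33%, the section should give the method and the list of tests that produce it.

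The cost is one or two sentences and no extra patients. The secondary threshold becomes less strict: familywise error over the two pairs stays at or below 5%, but the chance of any false positive across the pooled test and both pairs rises from about 5.7% to about 6.9%.

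If control over all three tests is wanted, closed testing is an option: each pair at 5% only after a significant pooled test. The price is that no pairwise claim is possible if the pooled test fails, and power improves only if the untreated-arm difference is about as large as the sham difference.

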### 6.3.5 Handling missing data

No imputation strategy will be realized: the analysis being an analysis by mixed models, the parameters are estimated without bias in case of missing data under the assumption that these data are missing randomly.

### 6.3.6 Software used

Statistical analysis will be carried out by the Clinical Epidemiology Unit by [name] under the responsibility of [name] using the SAS 9.2 and/or R.2.13 software.

1. Licciardone et al, Osteopathic manipulative treatment of somatic dysfunction among patients in the family practice clinic settings : a retrospective analysis, JAOA, Vol 105, No12, Dec 2005, 537-543. [↑](#footnote-ref-1)
